### Plans to promote participant retention and complete follow-up {25b}

To promote participant retention and complete follow-up, the study visits are scheduled to coincide with routine clinical appointments whenever possible, with additional visits for necessary measurements of clinical activity and biomarkers. Study staff follow up on missed appointments promptly. Efforts are made to maintain regular communication with participants to encourage continued participation and ensure data completeness.

### Data management {26}

All data are transferred from source documents into the electronic Case Report Form (eCRF) Clincase. Data quality is ensured through range and consistency checks, and key variables are verified by independent monitoring.

### Confidentiality {33}

Participant data are pseudonymised, with access restricted to authorised personnel, and securely stored in compliance with data protection regulations.

## Statistical methods

### Statistical methods for primary and secondary outcomes {27a}

The null hypothesis is as follows: The use of 25 mg SCMTX is not superior to 25 mg POMTX weekly in patients with active RA, previously treated with POMTX.

The primary endpoint, defined as the proportion of patients achieving CDAI remission at week 24, will be compared between treatment groups using a *χ*^2^ test. A Fisher’s exact test will be used if the endpoint occurs in fewer than five patients in any group. Superiority of the subcutaneous MTX arm will be tested at a two-sided alpha level of 0.05.

Secondary categorical outcomes will be analysed using *χ*^2^ tests (or Fisher’s exact tests where appropriate), and non-normally distributed continuous outcomes will be analysed using the Mann–Whitney *U* test. For categorical variables, absolute frequencies and percentages will be reported. Time to CDAI remission will be analysed using Kaplan–Meier curves, reporting medians and interquartile ranges, and compared between treatment groups using a log-rank test.

Secondary endpoints will be tested in a pre-specified stepwise hierarchical order until the first non-significant result is reached. All outcomes tested thereafter will be considered exploratory (hypothesis-generating). The following sequence for secondary endpoint testing will be utilised: Proportion of CDAI remission at week 12 > CDAI low disease activity (≤ 10) at week 24 > CDAI low disease activity (≤ 10) at week 12 > ACR70% response at week 24 > ACR50% response at week 24 > Difference in change of patient global assessment > HAQ-DI > CRP at week 24 respectively. An early analysis of the main secondary endpoints will be performed at week 12. All other secondary outcomes will be analysed exploratorily.

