### Sample size {19}

Based on literature, the primary endpoint (CDAI ≤ 2.8, i.e. remission) is expected to be achieved by 5% of patients included in the p.o. dose arm, and by 20% in the s.c. arm of the trial [14, 32, 33]. Patients will be randomised in a 1:1 ratio, resulting in an expected sample size for the main outcome of 76 per group (based on *χ*^2^ statistics) with 80% power and a two-sided alpha of 0.05. To account for a conservative 16% dropout rate, the study aims to include 182 patients in total.

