### Sequence generation: type of randomisation {21b}

Patients are randomised in a 1:1 ratio, using stratified randomisation by study centre. Details of the software’s randomisation algorithm and any blocking to reduce predictability are documented internally and are not accessible to personnel enrolling participants or assigning interventions.

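### The primary test switches to Fisher's exact test on observed remissions rather than expected counts, so near-equivalent results can get opposite verdicts; it also leaves out the stratification factor, centre

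*Protocol article*

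**What the plan says.** Under Statistical methods for primary and secondary outcomes {27a}, the proportion in CDAI remission at week 24 is compared by a chi-square test. Fisher's "exact test will be used if the endpoint occurs in fewer than five patients in any group". Superiority of the subcutaneous arm "will be tested at a two-sided alpha level of 0.05". Binary secondary outcomes get the same pair of tests, with the condition for Fisher left to what is appropriate.

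Sample size {19} rests on chi-square statistics. Remission "is expected to be achieved by 5% of patients included in the p.o. dose arm, and by 20% in the s.c. arm", "resulting in an expected sample size for the main outcome of 76 per group", "with 80% power and a two-sided alpha of 0.05". A 16% dropout allowance brings the total to 182.

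Sequence generation {21b} states: "Patients are randomised in a 1:1 ratio, using stratified randomisation by study centre". Centre does not appear in the primary test. The sections on analysis sets {27b} and missing data {27c} count participants who discontinue or are lost as non-responders.

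**The concern.** The usual reason to replace chi-square by Fisher is a small expected cell count, which in a balanced trial depends on the total number of remissions. The stated rule looks instead at the smaller arm's observed remissions. The two differ most when one arm does poorly and the other well, which is what this trial is designed to find. With 5% expected in the oral arm, the observed count will sit around the threshold of five, so the design assumptions make it close to a coin toss which test decides the primary question.

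At stake is the coherence of the primary verdict. Two results with the same absolute difference can be judged by different tests and come out on opposite sides of 0.05, with the smaller relative effect declared significant. A lesser issue is that randomisation is stratified by centre while the test is crude, so analysis and design do not match.

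**Working it through.** **Inputs.** From Sample size {19}: 5% oral, 20% subcutaneous, 80% power, two-sided 0.05, 1:1 allocation, 16% dropout, 182 in total. From {27a}: Fisher if either arm has fewer than 5 observed remissions, otherwise chi-square. From {27c}: dropouts are non-responders. I assume equal arms of 91.

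**1. The plan's own figure.** With pooled variance and no continuity correction:

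n = [1.96·√(2·0.125·0.875) + 0.842·√(0.05·0.95 + 0.20·0.80)]² / 0.15² = 75.1, so 76 per group. Then 76/0.84 = 90.5, so 91 per group and 182 in total. The sample size reproduces.

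**2. How often the switch fires.** Expected oral remissions are 91 × 0.05 = 4.55. If 16% of each arm count as failures, the rates become 0.84 × 5% = 4.2% and 0.84 × 20% = 16.8%, and expected oral remissions are 3.82. With equal arms, the smallest expected cell is half the total number of remissions. Exact binomial enumeration of all tables gives:

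| Scenario | Fisher triggered by stated rule | Smallest expected count < 5 |
|---|---|---|
| 91 per arm, 5% vs 20% | 52% | 0.04% |
| 91 per arm, 4.2% vs 16.8% | 66% | 0.5% |
| 76 per arm, 5% vs 20% | 67% | 0.5% |

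**3. Neighbouring results at 91 per arm.** For equal arms, chi-square = 2n(b − a)² / [t(2n − t)], where a and b are the remissions per arm and t = a + b.

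- 4 vs 12: 182·64 / (16·166) = 4.39, p = 0.036; smallest expected count 16/2 = 8. The rule sends this to Fisher, p = 0.064: not significant.
- 5 vs 13: 182·64 / (18·164) = 3.95, p = 0.047; smallest expected count 9. The rule keeps chi-square: significant. Fisher would give 0.080.

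The difference is 8/91 in both, and the ratio falls from 12/4 = 3.0 to 13/5 = 2.6. Chi-square alone calls both significant and Fisher alone calls neither. Only the switch separates them, and it favours the weaker relative effect.

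**4. Power and type I error by exact enumeration.**

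| Scenario | Stated rule | Chi-square throughout | Switch on expected count < 5 |
|---|---|---|---|
| Power, 91 per arm, 5% vs 20% | 88.6% | 89.4% | 89.4% |
| Power, 91 per arm, 4.2% vs 16.8% | 80.0% | 82.8% | 82.7% |
| Power, 76 per arm, 5% vs 20% | 80.2% | 83.3% | 83.2% |
| Type I error, 91 per arm, common 5% | 1.9% | 4.2% | 2.8% |

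At 91 per arm, the stated rule's type I error peaks at about 0.052 for common rates up to 35%, the same as plain chi-square. The two disagree on the verdict in 0.8% of trials at design rates and 2.8% at diluted rates.

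**5. Centre.** Simulation with 7 centres of 26 patients, 3000 runs per scenario and an assumed centre SD of 0 to 1 on the logit scale: a Cochran-Mantel-Haenszel test by centre gains 0 to 1.6 power points over the crude test. At SD 1 the crude test's type I error is 0.034. The documents give no centre variation, so this range is illustrative.

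**The case against.** The strongest defence is that the rule is prespecified, mechanical and conservative, and seldom changes the answer. That largely stands. With the subcutaneous arm ahead at 91 per arm, the rule and plain chi-square disagree on only six tables: 0 vs 4, 0 vs 5, 1 vs 7, 2 vs 9, 3 vs 10 and 4 vs 12. All are borderline. An expected-count switch would also send the first three to Fisher, so that correction alters only the last three. Being triggered in half of trials is not the same as altering half of verdicts.

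Stronger readings are tempting, and the documents do not support them:

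- *The trial loses its planned power.* At 91 per arm the rule gives 88.6% at design rates and 80.0% when diluted, so the stated 80% is met in both. Larger losses need lower rates than the protocol assumes, or 76 per arm with diluted rates (68.5%), which counts dropout twice.
- *The switch makes false positives likelier.* It does not: the rule is conservative at low rates.
- *One extra oral remission can by itself turn failure into success.* At 91 per arm the smallest significant subcutaneous count is 13 for both 4 and 5 oral remissions. The inconsistency is between results with equal differences, not at a fixed subcutaneous count.
- *Leaving out baseline CDAI is an error.* It is not a stratification factor, so its absence contradicts nothing. Any gain rests on a prognostic strength the documents do not give, and covariate adjustment may be in the analysis plan, which is not shown.

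A crude test after centre-stratified randomisation also remains valid, only slightly conservative. What survives is that the trigger itself is stated, is tied to the wrong quantity, and produces inconsistent verdicts where results are likely to fall.

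**Conclusion.** The point holds as a mis-specified decision rule for the primary endpoint, and it should be fixed. Under the protocol's own rates Fisher displaces the test used for sizing in 52% to 66% of trials at 91 per arm, almost never because an expected count is small, and it can reverse the verdict between results with the same risk difference. The cost is modest: 0.8 power points at design rates and 2.8 when diluted, with no material inflation of type I error. Omitting centre is a secondary mismatch between design and analysis.

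The trigger and power figures assume arms of exactly 91 and, for the diluted case, 16% non-response by dropout in both arms. The centre figures rest on assumed centre effects. The sample size of 76 per group and 182 in total is correct.

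**What to change.** Before database lock, prespecify one primary test and delete the observed-count switch. The preferred choice is a Cochran-Mantel-Haenszel test stratified by centre, reported with the Mantel-Haenszel risk difference and its 95% confidence interval; this also brings the analysis into line with the randomisation. If a crude test is kept, use Fisher only when an expected cell count is below 5.

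State the same rule for the binary secondary endpoints, since week-12 CDAI remission heads the testing hierarchy and low disease activity, ACR70 and ACR50 follow.

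Adjustment for baseline CDAI can be added as an optional supportive analysis. Crossing it with centre in the primary test is not advisable: two CDAI levels by 7 centres makes 14 strata for only about 19 to 23 expected remissions (91 × 0.21 to 91 × 0.25).

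The cost is wording in the protocol and analysis plan. No new data or patients are needed, and the last patient's visit is not expected until May 2027.

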## Assignment of interventions: blinding

### Who will be blinded {24a}

Joint assessors performing outcome measurements are blinded to participants’ study assignments. Patients, care providers and personnel performing randomisation are not blinded.

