### Interim analyses {28b}

No formal interim analyses or stopping guidelines are planned. The early analysis conducted at week 12 is limited to selected secondary endpoints and will not influence decisions regarding trial continuation or termination.

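### The secondary test sequence is not tied to the primary endpoint and can start at an early week-12 analysis, and access to that analysis is not restricted while some patients are still heading to week 24

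*Protocol article*

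**What the plan says.** In the protocol article, section {27a} (statistical methods for primary and secondary outcomes) says of the primary comparison: "Superiority of the subcutaneous MTX arm will be tested at a two-sided alpha level of 0.05". For the secondaries it says: "Secondary endpoints will be tested in a pre-specified stepwise hierarchical order until the first non-significant result is reached". The listed order starts with CDAI remission at week 12, followed by low disease activity at week 24, low disease activity at week 12, and then ACR and continuous outcomes. The same paragraph adds: "An early analysis of the main secondary endpoints will be performed at week 12".

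Section {28b} (interim analyses) says that no formal interim analysis is planned. It describes the look this way: "The early analysis conducted at week 12 is limited to selected secondary endpoints". It also bars the look from bearing on whether the trial continues or stops.

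On blinding, section {24a} says: "Patients, care providers and personnel performing randomisation are not blinded". Joint assessors are blinded and, under {24b}, have no access to patient data or case report forms. Section {28a} says that there is no independent data and safety monitoring board.

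**The concern.** There are two separate issues.

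**Gating.** Section {27a} states where the secondary sequence starts and what stops it. A non-significant primary is not among the things that stop it. Read literally, the trial has two entry points, each at 0.05: the primary, and the first step of the secondary chain. The early analysis makes this more than a matter of wording, because the first step is a week-12 endpoint and could be declared significant before any week-24 result is known. What is at stake is a confirmatory claim on a secondary endpoint in a trial whose primary fails, without 5% control over the whole set.

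**Access.** The restriction in {28b} deals with stopping. It does not say who may see the results while follow-up continues. The week-12 items in the sequence use CDAI, the same index as the primary. The patient global score comes from an unblinded patient, and the evaluator global score may also be unblinded. Section {15b} lists investigator judgement among the reasons for discontinuing treatment, and a premature end of study counts as non-response. If week-12 results by arm became known, they could influence those parts of the primary endpoint in patients still to be assessed.

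**Working it through.** **The plan's own figure.** The inputs are in section {19}. Planned rates: "expected to be achieved by 5% of patients included in the p.o. dose arm, and by 20% in the s.c. arm of the trial". Error levels for the test: "with 80% power and a two-sided alpha of 0.05". Allocation between the arms: "Patients will be randomised in a 1:1 ratio". The two-proportion formula with pooled variance and no continuity correction gives 76 per arm (power at 76: 80.5%). Allowing for 16% dropout, 76 / 0.84 = 90.5, so 91 per arm and 182 in total. The stated sample size reproduces.

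**Family-wise error without a gate.** The article states no figure, so this follows from its rules. A fixed sequence holds its own error at 0.05, and so does the primary.

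- Upper bound: 0.05 + 0.05 = 10%.
- Independent tests: 1 − 0.95² = 9.75%.
- Correlated tests: 1 − P(|Z₁| < 1.96 and |Z₂| < 1.96), with Z₁ and Z₂ bivariate normal with correlation ρ between the primary and first-secondary statistics. The document gives no ρ, so a range is shown:

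| ρ | Family-wise error | False claims favouring s.c. only |
|---|---|---|
| 0 | 9.75% | 4.9% |
| 0.3 | 9.5% | 4.8% |
| 0.5 | 9.1% | 4.5% |
| 0.7 | 8.3% | 4.2% |
| 0.8 | 7.8% | 3.9% |
| 0.9 | 7.0% | 3.5% |

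**The same check with the stated tests.** The chi-square test, replaced by Fisher's test when either arm has fewer than five events, was simulated with 91 per arm, equal rates in both arms, latent correlation 0 to 0.8, and 20,000 runs per setting:

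- common remission rate 12.5% to 20%: 8.5% to 9.5%;
- common remission rate 5%: 3.4% to 4.0%, because Fisher's test is conservative with so few events.

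The primary's own error was about 5% or less in every setting.

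**With a gate.** If the sequence opens only after a significant primary, no false secondary claim can be made when the primary is truly null unless the primary test has itself erred. If the primary effect is real, the chain holds its own 5%. Family-wise error is therefore at most 5.0%.

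**Patients still in follow-up at the early look.** The article gives no calendar date for it. Assume that it is run when the last patient reaches week 12, and that accrual is even from 12 August 2024 to the end of November 2026. That is 840 days, or 120 weeks. Patients between weeks 12 and 24: 182 / 120 × 12 = 18.2, or about 10%. The number is higher if the look is earlier or if recruitment is weighted towards the end.

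**The case against.** The article is condensed and says that the full protocol and analysis plan are published with it. A gating sentence, the date of the early look and its access rules could be there. The article never says that the sequence runs if the primary fails, and it makes no family-wise claim. This stands to a degree: the missing gate is an inference from silence. But {27a} does not merely leave the hierarchy open. It states the start, the order and the stopping rule, and that text gives two ungated entries.

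Stronger readings are tempting, and the document does not support them:

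- *That the early look inflates the primary's 0.05.* It does not. It is confined to secondaries and has no stopping rule. The excess error comes from the missing gate and concerns the combined family.
- *That the article contradicts itself by denying an interim analysis and then doing one.* The restriction in {28b} reconciles the two as far as stopping goes.
- *That family-wise error is about 10%.* That is the ceiling. Both tests use CDAI remission in the same patients, so the statistics are correlated.
- *That the primary endpoint is unblinded.* Both joint counts are made by blinded assessors. The patient global score is unblinded. The article does not say directly whether the evaluator global score is, though its discussion says that only joint assessment is blinded.
- *That physicians freely decide rescue.* Section {15b} sets numerical triggers, one of which rests wholly on the blinded joint counts. Investigator judgement remains as a separate ground for discontinuation.
- *That the early look is stated to compare the arms.* It is not stated outright. It is a strong inference, since {27a} describes secondary analyses as comparisons between groups.
- *That one event would decide the trial.* At 91 per arm, 4 against 12 gives Fisher p = 0.064 and 4 against 13 gives p = 0.039, but any discrete test behaves this way at its boundary. Near the planned rates, 4 against 15 gives p = 0.0135.

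Open-label global scores can also be biased without any early look. The extra effect of knowing week-12 results has not been quantified.

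**Conclusion.** The point holds in two limited parts.

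First, the secondary sequence as written is not conditional on the primary and can begin before the primary is known. The resulting family-wise error is about 7% to 9.5% for correlations of 0.9 to 0.3, 9.75% under independence, and below 5% if remission is near 5% in both arms. The correlation and the common remission rate are assumptions. The test of the primary endpoint is sound at its stated level.

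Second, the early analysis is kept from stopping decisions, but access to its results is not restricted. With no independent board and a partly unblinded primary endpoint, this leaves room for operational bias in the patients not yet at week 24: about 18 of 182 under even accrual and a look at the last patient's week 12. This is a risk that the plan leaves open. The documents do not show that bias will occur, and its size cannot be estimated from them. Both parts should be corrected, and neither threatens the design.

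**What to change.** 1. Add to {27a}: *The secondary sequence is tested only if the primary test is significant at two-sided 0.05.*
2. State that confirmatory tests of week-12 endpoints are done only at the final analysis.
3. Hold between-arm week-12 results until the last week-24 visit and database lock. If an early look is needed, keep the results by arm with a firewalled statistician and release pooled data only.
4. Align {28b} with these rules, stating when the early analysis is run and who sees it.

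The cost is a wording change in the protocol and analysis plan, and week-12 results by arm that come about three months later (12 weeks, from roughly late February to May 2027 on the stated timelines). The primary keeps its full 0.05, so 76 per arm and 182 in total are unchanged.

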### Who will be included in each analysis {27b}

Two analysis sets are defined. The (modified) intention-to-treat (ITT) population includes all randomised participants who received at least one dose of study drug and will be used for all primary analyses. Participants will be analysed according to their allocated treatment group. Non-responder imputation will be applied for patients who discontinue the study or are lost to follow-up over the 24-week study period. The per-protocol population comprises participants who received at least one dose of study drug and did not have major protocol violations that could affect evaluation of the treatment effect on the primary objective. Analyses in this population will be performed as secondary analyses. The time-to-event analysis of time to CDAI remission will not follow a strict ITT approach, as the Kaplan–Meier method accounts for participants who discontinue or are lost to follow-up through censoring.

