## Eligibility criteria for participants {14a}

The inclusion criteria are as follows:Men and women, ≥ 18 years of age, capable of understanding and signing an informed consent (including sufficient literacy and proficiency in the local language) and following the study procedures.Patients with RA according to the 2010 ACR/EULAR classification criteria.Ongoing conventional therapy with oral MTX (between ≥ 10 mg and 25 mg weekly) for ≥ 3 months with stable dosing, and clinical and laboratory tolerance of this treatment for at least 12 weeks.CDAI > 2.8 + at least 1 clinically swollen joint (on 28-joint count).Willingness to increase MTX dosing and change the route of administration according to study procedures.

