The exclusion criteria are as follows:Inflammatory rheumatic diseases other than RA.Ongoing or previous therapy with any targeted synthetic DMARDs (tsDMARD) or biological Disease-Modifying Anti-Rheumatic Drug (bDMARD) with the exception of any TNFα inhibitor in a stable dose and interval for at least 4 months. We allow ongoing or previous therapy with a conventional synthetic DMARD (csDMARD) with a stable dose in the past 4 months.Use of glucocorticoids (GC) unless on stable oral dose ≤ 10 mg for at least 4 weeks prior to study inclusion.Patients using NSAIDs, unless taken at a stable dose for ≥ 2 weeks prior to study inclusion.Intraarticular GC treatment in the last 8 weeks.Patients with significant and clinically relevant MTX-drug toxicity as judged by the investigator.Elevated liver enzymes (aspartate transaminase (AST) and/or alanine transaminase (ALT)), and/or alkaline phosphatase (AP), and/or gamma-glutamyl transferase (GGT) above two times the upper limit normal (ULN).Reduced kidney function (glomerular filtration rate (GFR) < 60 mL/min/1.73 m^2^).Haematologic abnormalities (grade 2 or 3: anaemia, leukopenia, thrombocytopenia).Stomatitis under treatment with MTX.Known history of recurrent/serious infections in the previous 2 months (such as, but not limited to, hepatitis, pneumonia, or pyelonephritis).A positive HBs antigen and/or hepatitis C virus (HCV) test at screening visit.Ongoing or recurring opportunistic infections (e.g. herpes zoster, cytomegalovirus, pneumocystis, aspergillosis, histoplasmosis, or mycobacteria) as judged by the investigator.Women of childbearing potential without the use of adequate birth control measures (e.g. abstinence, oral contraceptives, intrauterine device, barrier method with spermicide, implantable or injectable contraceptives or surgical sterilisation) and willing to continue this precaution for the duration of the study until 6 months after receiving the last medication.Current signs or symptoms of severe, progressive or uncontrolled renal, hepatic, haematologic, gastrointestinal, endocrine, pulmonary, cardiac, neurologic, or cerebral disease, as judged by the investigator.Being unable or unwilling to undergo multiple venipunctures because of poor tolerability or lack of sufficient venous access.Being unwilling or unable to perform s.c. injections.Presence of a transplanted solid organ (except for a corneal transplant > 3 months prior to screening).Women who are pregnant, nursing or planning pregnancy during the study and 6 months after the individual study completion.History of alcohol or substance abuse within the preceding 6 months.Any medical or psychological condition that, judged by the investigator, would interfere with the safe completion of the trial.Immunisation with a live/attenuated vaccine within 12 weeks prior to baseline or potential need to receive a live vaccine during the course of the study.Active participation in any other interventional study.

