### How missing data will be handled in the analysis {27c}

For the primary endpoint, non-responder imputation will be applied to all participants who discontinue the study or are lost to follow-up. In time-to-event analyses, missing data due to dropout will be handled by censoring. No additional imputation methods are planned.

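### The primary analysis set leaves out randomised patients who take no dose, although allocation is open, and no analysis set in the protocol covers everyone randomised

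*Protocol article*

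**What the plan says.** Section {27b} defines two analysis sets. The first, labelled a modified intention-to-treat population, "includes all randomised participants who received at least one dose of study drug and will be used for all primary analyses". Within it, "Participants will be analysed according to their allocated treatment group". The second, per-protocol, also requires at least one dose and in addition no major protocol violation.

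For missing outcomes, section {27c} says of the primary endpoint that "non-responder imputation will be applied to all participants who discontinue the study or are lost to follow-up", and then that "No additional imputation methods are planned".

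On blinding, section {24a} says: "Patients, care providers and personnel performing randomisation are not blinded". Only the joint assessors are blinded.

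Three eligibility criteria in section {14a} bear on who might fail to start. All patients come in on "Ongoing conventional therapy with oral MTX (between ≥ 10 mg and 25 mg weekly) for ≥ 3 months with stable dosing". Inclusion requires "Willingness to increase MTX dosing and change the route of administration according to study procedures". Exclusion covers "Being unwilling or unable to perform s.c. injections".

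**The concern.** A dosed-patients set is usually defended on the ground that starting treatment cannot depend on the arm, because nobody involved knows the arm. That defence is not available here. A patient who learns the allocation and then declines the first dose leaves the primary analysis, and the reason for declining may be the allocation itself.

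The imputation rule does not repair this. A patient who stops after one dose counts as a failure. A patient who refuses the first dose disappears from the denominator, because the dose condition acts before imputation can. The exclusion also gains nothing: the endpoint is binary and absent outcomes already count as failures, so never-dosed patients can be kept without any data on them.

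At stake is whether the primary comparison is between the groups as randomised. With a 5% remission rate expected in the oral arm, events are few, and a borderline result could turn on a handful of patients.

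**Working it through.** **Inputs from the article.** Expected remission 5% oral and 20% subcutaneous, 1:1 allocation, 80% power, two-sided alpha 0.05, 76 per group, 16% dropout, 182 in total (section {19}). The primary test is chi-square, or Fisher's exact if a group has fewer than five events (section {27a}).

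**Input that the article does not give.** The number of never-dosed patients, k. I assume 0 to 9 of 91 (0 to 10%), all in one arm, which is the extreme case for bias.

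**The plan's own figure.** With pooled variance and p̄ = 0.125:

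n = [1.960·√(2·0.125·0.875) + 0.842·√(0.05·0.95 + 0.20·0.80)]² / 0.15² = 75.1, so 76 per group.

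76/0.84 = 90.5, so 91 per arm and 182 in total. The sample size is reproduced.

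**Effect on the test.** With a of n₁ oral and b of n₂ subcutaneous patients in remission, c = n₁ − a, d = n₂ − b and N = n₁ + n₂, the uncorrected statistic is χ² = N(ad − bc)² / [n₁·n₂·(a + b)·(c + d)].

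Take 8/91 oral v 17/91 subcutaneous, all randomised, never-dosed patients counted as failures:

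- ad − bc = 8·74 − 17·83 = −819
- χ² = 182·819² / (91·91·25·157) = 3.756, p = 0.053

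Remove one subcutaneous non-starter:

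- ad − bc = 8·73 − 17·83 = −827
- χ² = 181·827² / (91·90·25·156) = 3.876, p = 0.049

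Other counts, by the same formula:

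| Remissions, oral v s.c. | All randomised (91 v 91) | Non-starters removed from | p after removal |
|---|---|---|---|
| 8 v 17 | 0.053 | s.c., k = 3, 5 | 0.042, 0.036 |
| 6 v 14 | 0.058 | s.c., k = 3, 5 | 0.048, 0.042 |
| 5 v 13 | 0.047 | s.c., k = 2, 6 | 0.042, 0.032 |
| 5 v 12 | 0.075 | s.c., k = 2, 6 | 0.067, 0.053 |
| 7 v 16 | 0.045 | oral, k = 3, 5, 9 | 0.054, 0.062, 0.080 |
| 5 v 18 | 0.004 | s.c., k = 9 | 0.0015 |
| 5 v 18 | 0.004 | oral, k = 9 | 0.008 |

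Removal can carry a result across 0.05 in either direction (8 v 17 and 6 v 14 one way, 7 v 16 the other). It need not do so (5 v 13 and 5 v 12), and near the planned effect (5 v 18) it changes nothing.

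**False-positive risk if all non-starters are in the subcutaneous arm.** Suppose the true remission rate among all randomised patients is equal in both arms and never-dosed patients are failures. Subcutaneous starters then remit at the common rate times 91/(91 − k). Exact binomial enumeration, using the protocol's test rule, gives this chance of a significant result in favour of the subcutaneous arm:

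| Common rate | k = 0 | k = 2 | k = 5 | k = 9 |
|---|---|---|---|---|
| 5% | 1.0% | 1.9% | 1.9% | 2.6% |
| 10% | 2.1% | 2.6% | 3.1% | 3.8% |
| 20% | 2.5% | 3.0% | 3.8% | 5.6% |

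**Cost in power of keeping everyone.** If starters remit at 20% v 5% and k subcutaneous patients never start, the all-randomised difference is 0.20·(91 − k)/91 − 0.05.

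| k | Difference, all randomised (points) | Power, all randomised | Power, dosed set |
|---|---|---|---|
| 0 | 15.0 | 88.6% | 88.6% |
| 2 | 14.6 | 87.0% | 88.5% |
| 5 | 13.9 | 84.3% | 88.3% |
| 9 | 13.0 | 80.1% | 86.7% |

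Even with nine non-starters in the subcutaneous arm, 182 patients still give 80% power.

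**The case against.** The case for leaving the text alone has several good parts. The set is openly labelled as modified, patients are kept in their allocated arm, and every dosed patient who drops out counts as a failure, so the larger source of differential loss is already handled conservatively. Section {14a} screens out patients who would refuse a change of route or could not inject. Table 2 places the eligibility check, randomisation and first drug distribution at the same baseline visit, which leaves little time for second thoughts. At the planned effect the conclusion does not move, and the examples that cross 0.05 are chosen borderline counts with every non-starter in one arm.

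All of this stands as an argument that the numbers will be small. It does not show that there will be none: willingness stated before allocation does not guarantee a first dose after it. Disclosing the set does not restore the patients it removes.

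A reader might go further and infer that the exclusions will fall mainly on the subcutaneous arm and so favour the trial's hypothesis. There is an argument for that: everyone already takes oral methotrexate, so tablets are the easier start. But it is plausibility only. The article reports no non-starters by arm, its entry criteria screen out those unwilling to inject, and patients who hoped for the new route and drew tablets might equally withdraw, which would reverse the bias. The documents do not support a one-directional claim.

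**Conclusion.** The point holds as a weakness in the primary analysis set, with the direction of bias unknown. Membership depends on a post-randomisation event that can be influenced by a known allocation, imputation does not reach those excluded, and both defined sets share the dose condition.

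The effect is probably small. It could decide the verdict only if the result is borderline and non-starters are concentrated in one arm; a result near the planned 5% v 20% is safe either way. These sizes rest on the assumed 0 to 9 non-starters, all in one arm. Because the remedy is nearly free, the change is worth making.

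**What to change.** In section {27b}, and in the analysis plan if it repeats the definition, make the primary set all randomised patients, analysed in their allocated arm. State that patients who never take a dose count as non-responders for the primary endpoint. Keep the dosed set for safety and as a sensitivity analysis of the primary endpoint. Report the number of never-dosed patients in each arm, with reasons.

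The cost is a sentence or two of text. No extra data are needed and the sample size of 182 stands. The downside is that remission in an arm with non-starters may look slightly lower, and if they are in the subcutaneous arm some power is lost, as tabulated above. Section {Trial status} plans the last patient's first visit for the end of November 2026, and the change should be made before outcome data are compared by arm.
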